### **6.2 Secondary Endpoints**

Secondary endpoints will include the rate of symptom remediation in OBVAT+SCC group compared to SCC alone, change in vision function, and fMRI measures over the duration of the intervention.

### **6.3 Statistical Methods**

#### **6.3.1 Baseline Data**

Baseline and demographic characteristics will be summarized by standard descriptive summaries (e.g. means and standard deviations for continuous variables such as age and percentages for categorical variables such as gender).

#### **6.3.2 Efficacy Analysis**

The primary analysis will be based on an intention to treat approach and will include all subjects randomized at their initial assessment.

The primary efficacy endpoint will be the change in composite clinical parameters of near point of convergence and positive fusional vergence between the initial assessment and the outcome visits. A repeated measures ANOVA will be used to assess the clinical parameters as well as the chi-squared test using predetermined published optometric benchmarks for improvement.

Secondary endpoints will include the rate of symptom remediation in OBVAT+SCC group compared to SCC alone, change in vision function, and fMRI measures between the start and end of the treatment phase.

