### **4.2 Study Treatment Phase**

All subjects who are deemed eligible and interested in participating in the study after the screening will complete a written or electronic informed consent at their screening visit, before any study procedures take place. Subjects will then complete an initial assessment prior to the start of the treatment phase. The initial assessment may take place on the same day as the screening visit after informed consent has taken place.

For arm 1, the study treatment phase will consist of 12 one-hour OBVAT sessions bi-weekly followed by Outcome Visit 1. After completion of Outcome Visit 1, arm 1 subjects will complete 4 additional one-hour OBVAT sessions bi-weekly followed by Outcome Visit 2.

For arm 2, subjects will complete 6 weeks of SCC followed by Outcome Visit 1. After completion of Outcome Visit 1, arm 2 subjects will complete 16 one-hour sessions of OBVAT bi-weekly followed by Outcome Visit 2.

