#### **4.3.1 Early Termination Study Visit**

Subjects will be withdrawn if their eligibility status changes such that it is no longer safe for them to complete the fMRI. If subjects choose to withdraw from the study, all of their longitudinal data will be excluded from the final data analysis. If initial baseline assessments are complete a group level comparison will be conducted with this current PPCS-CI data and the already collected TYP-CI and control data.

---

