### **6.4 Sample Size and Power**

We expect that approximately 200 subjects will be enrolled to produce 150 subjects who finish the protocol and data does not suffer motion artifacts which can cause data to be

---

omitted from group level analyses. The sample size calculation was performed using paired *t*-tests with equal variance for TYP-CI patients from both placebo therapy and OBVAT. Our published pilot data had an estimated correlation of -0.3, 0.9, -0.4, and -0.3 for CISS, NPC, PFV, beta weight from oculomotor vermis respectively. This gave a standard deviation of the difference (OBVAT- placebo/sham therapy) to be 19, 2, 19, and 27. Assuming 80% power, Alpha= 0.05, and adjusting for an 80% retention rate and 15% data loss due to motion artifacts during fMRI experiments, results in the number of subjects needed to be 37, 6, 37, 46 respectively. Using the maximum sample size for all conditions and to be satisfied, yields a cohort size of 46 per arm. We rounded the number of participants to 50 PPCS-CI for each arm.

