## **6.5 Interim Analysis**

A trained vision therapist will monitor and administer the OBVAT to ensure that all participants complete it safely. The treating provider will determine if it is appropriate to terminate the OBVAT for any subjects that show an extended increase in symptoms.

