#### **7.1.1 Treatment Compliance and Adherence**

Subjects must complete all of their OBVAT sessions and assessments to receive full compensation for participation in the study. Outcome visits will not be scheduled until the subject has completed all of their OBVAT sessions, and compensation will be dispensed upon completion of each outcome visit.

---

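### The primary analysis is declared intention-to-treat, but the repeated measures ANOVA named for it would, in its classical form, drop subjects measured at Outcome Visit 1 who have no Outcome Visit 2

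*Protocol*

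**What the plan says.** Section 6.3.2 of the protocol fixes the analysis population: "The primary analysis will be based on an intention to treat approach and will include all subjects randomized at their initial assessment". It defines the primary endpoint as change in the composite of near point of convergence and positive fusional vergence "between the initial assessment and the outcome visits", in the plural. It then names the method: "A repeated measures ANOVA will be used to assess the clinical parameters", together with a chi-squared test against published optometric benchmarks.

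Other sections decide who will have a full set of visits:

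- Section 4.2 gives arm 1 four further OBVAT sessions between the two outcome visits. For arm 2: "After completion of Outcome Visit 1, arm 2 subjects will complete 16 one-hour sessions of OBVAT bi-weekly followed by Outcome Visit 2".
- Section 7.1.1: "Outcome visits will not be scheduled until the subject has completed all of their OBVAT sessions".
- Section 6.5: "The treating provider will determine if it is appropriate to terminate the OBVAT for any subjects that show an extended increase in symptoms".
- Section 4.3 also lets the investigator discontinue subjects for poor adherence.
- Section 4.3.1: "If subjects choose to withdraw from the study, all of their longitudinal data will be excluded from the final data analysis".
- Section 6.4 sizes the trial "adjusting for an 80% retention rate and 15% data loss due to motion artifacts".

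The synopsis names a Wilcoxon signed test and a paired t-test, and speaks of interactions between groups and time periods before and after therapy.

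**The concern.** The stated population and the stated method do not fit together. In its classical least-squares form, repeated measures ANOVA works on subjects with a value at every visit in the model. The paired t-test and the Wilcoxon signed test in the synopsis also need both members of each pair. No method named in the protocol keeps a subject with a partial visit record in an analysis spanning both outcome visits.

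The design makes this matter. OBVAT plus standard care is compared with standard care alone only up to Outcome Visit 1, since arm 2 then starts OBVAT. Requiring Outcome Visit 2 makes membership of the randomised comparison depend on something that happens later and asks more of one arm than the other. Observed Outcome Visit 1 values would be discarded. If the reason for stopping is related to those values, the contrast could be distorted as well as less precise.

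The section 4.3.1 exclusion is a related but separate problem. It concerns subjects who choose to withdraw, and for them it contradicts the intention-to-treat statement outright. Subjects lost to follow-up, discontinued by the investigator or taken off OBVAT by their provider are not covered by that rule, yet the ANOVA could still drop them.

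**Working it through.** **The plan's own figure.** Section 6.4 gives 46 per arm, rounded to 50. It cannot be reproduced because no target difference is stated. It can only be inverted. Removing the inflation leaves 46 × 0.80 × 0.85 = 31.28. With a standard deviation of 27 for the difference and a paired normal approximation (two-sided 0.05 assumed, 80% power), the implied difference is 27 × (1.960 + 0.842) / √31.28 ≈ 13.5 for the imaging beta weight. This neither confirms nor refutes the 46. What the point uses is 50 per arm and 80% retention.

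**How many could be affected.** At 80% retention, 50 × 0.80 = 40 per arm finish, so 10 per arm do not. That 20% is not divided. It includes subjects lost before Outcome Visit 1, for whom no analysis has a post-baseline value, and subjects who choose to withdraw, already excluded by section 4.3.1. The share lost only through a missing Outcome Visit 2 is therefore anywhere from 0 to 20%.

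**What the method does.** In a simulated set of 100 subjects with three visits, 20 of them lacking the last, a standard classical repeated measures ANOVA routine rejected the data as unbalanced. Restricting to complete cases left 80 subjects and discarded 20 observed Outcome Visit 1 values. A random-intercept mixed model on the same data kept all 100 subjects and 300 − 20 = 280 observations. This shows only which data are retained.

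**Loss at random.** In units of the outcome SD, the standard error of a difference between two arms with a fraction p lost from each is √(2 / (50(1 − p))).

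- p = 0: √(2/50) = 0.200
- p = 0.05: √(2/47.5) = 0.205
- p = 0.10: √(2/45) = 0.211
- p = 0.15: √(2/42.5) = 0.217
- p = 0.20: √(2/40) = 0.224

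For a two-arm comparison set to 80% power at full numbers, the corresponding power is 78.0%, 75.7%, 73.3% and 70.7% at losses of 5, 10, 15 and 20%. This illustrates the precision given up. It is not a shortfall against the design, because section 6.4 has already inflated for 80% retention.

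**Loss related to the Outcome Visit 1 result.** Suppose the subjects lost from an arm average m SD above that arm's mean at Outcome Visit 1. The mean of those retained then shifts by −m × p/(1 − p). At p = 0.20 the factor is 0.20/0.80 = 0.25; at p = 0.05 it is 0.05/0.95 = 0.053. With equal p in both arms, the bias in the arm 1 minus arm 2 contrast is −(m₁ − m₂) × p/(1 − p). It is zero if the two arms lose the same kind of subject, and its sign follows m₁ − m₂. The protocol gives no information on m₁ or m₂. It does give a reason why they, and p itself, might differ: 4 further sessions in arm 1 against 16 in arm 2.

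**The case against.** The strongest reply is that section 6.3.2 says only that a repeated measures ANOVA will be used. It does not say complete cases, least squares, or one model requiring both outcome visits. A statistical analysis plan not at hand could define a likelihood-based fit, and estimation and missing-data rules are often left to it. This stands in part: complete-case deletion follows from the classical form of the named method and is not written in the protocol. But the protocol does fix a method and a population, and the method as ordinarily understood does not deliver the population. That goes beyond an omitted detail.

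Secondly, the synopsis refers to two periods, before and after therapy. If the randomised contrast were analysed as baseline against Outcome Visit 1 alone, a subject missing only Outcome Visit 2 would be complete and nothing would be lost. That reading is possible, but section 6.3.2 uses the plural and does not say each visit is analysed separately.

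Thirdly, section 6.5 allows OBVAT to be terminated without saying that the subject then forfeits Outcome Visit 2. That is correct. The forfeit follows only from reading section 7.1.1 literally.

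Fourthly, the chi-squared comparison does not need every visit, since benchmark status can be determined at Outcome Visit 1 alone. That also stands. The protocol simply does not say which visit it uses.

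Finally, a mixed model would not by itself restore intention-to-treat while section 4.3.1 removes withdrawers' data. This is right, and the fix has to cover both.

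**Conclusion.** The point holds as a mismatch between the declared population and the named method in section 6.3.2, and it should be corrected. It rests on reading the ANOVA in its classical form and the outcome visits as entering one model.

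Its size is bounded but not known: 0 to 20% of randomised subjects under the plan's retention figure. At the upper end, with 50 per arm and random loss, the standard error rises from 0.20 to about 0.22 SD.

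Two stronger readings are tempting, and the documents support neither:

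- A reader might infer that 20% of randomised subjects will go unscored for this reason. That figure is a ceiling which also covers withdrawers and losses before Outcome Visit 1.
- A reader might infer that the treatment effect will be overstated. The unequal session load makes differential loss plausible, but neither its strength nor its direction can be taken from the protocol, and the bias could be zero or of either sign.

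**What to change.** In section 6.3.2, replace the repeated measures ANOVA with a likelihood-based mixed model for repeated measures, with terms for arm, visit and arm-by-visit and an unstructured covariance. It should use every available visit from all randomised subjects, with the Outcome Visit 1 arm contrast as the primary estimate. State that the chi-squared benchmark comparison uses observed Outcome Visit 1 status whether or not Outcome Visit 2 takes place.

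Reconcile section 4.3.1 with the intention-to-treat statement in section 6.3.2, so that data collected before withdrawal stay in the intention-to-treat analysis. Align the synopsis with the revised method.

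The cost is analysis wording only: standard software, no new data and no added visits. The model relies on missingness at random given the observed values, and it cannot supply an Outcome Visit 1 value that was never measured.

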### **5.1.3 Other Evaluations, Measures**

- **Clinical Examination:** A standard optometric clinical exam that includes near point of convergence, positive fusional vergence, dissociated phoria, corrected visual acuity, unilateral cover test, stereopsis, monocular amplitude of accommodation, accommodative facility, vergence facility at near and far, negative fusion vergence, and eye movement and vestibular evaluation will be performed by a practicing, licensed optometrist.
  - **Patient-Reported Outcome Surveys:**
-

- CISS-Con
  - Vision Quality of Life with Time Survey (VisQual-T)
  - **VET:** An ISCAN eye tracker integrated into an Oculus head mounted display DK2 will track and record subjects' eye movement. The VET is about a 20 minute protocol comparing vergence steps at the beginning and end of a test while performing vergence steps and ramps, and saccades.
  - **VRS3:** An ISCAN eye tracker integrated into an Oculus head mounted display DK2 will track and record subjects' eye movement. The VRS3 is about a 15 minute protocol of vergence ramps, vergence steps, and saccades objective eye movements.
  - **Intervention:** This study involves a therapeutic intervention testing the effect of OBVAT in adolescent and young adults with PPCS-CI. Subjects will be randomly assigned to either an SCC+OBVAT or SCC only group using a pre-determined block randomization procedure.
    - **SCC+OBVAT:** subjects assigned to the SCC+OBVAT arm will attend bi-weekly OBVAT sessions with a trained and certified vision therapist. OBVAT has four phases. The first phase will be designed to manage some of the visual/vestibular issues common in PPCS-CI using eye movements associated with head and body movement. In phase 2, techniques will be used to stimulate gross convergence, positive fusional vergence and monocular accommodative therapy using Brock string, Vectograms, Computer Orthoptics and Lens Accommodative Rock, respectively. Once the subject can perform these tasks with ease, s/he will graduate to the third phase which is ramp fusional vergence and monocular accommodative therapy with Vectograms, Aperture Rule, Lifesaver Cards and Lens Accommodative Rock. The final stage will consist of jump fusional vergence and binocular accommodative facility. The initial phase is used to remediate vestibular issues if present but if there are no vestibular issues, then this phase will be omitted.

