## **6 STATISTICAL CONSIDERATIONS**

### **6.1 Primary Endpoint**

The primary endpoint will be the change in composite clinical parameters of near point of convergence and positive fusional vergence between the initial assessment and the outcome visits.

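### The primary analysis of change in NPC and PFV names no baseline covariate; using the initial-assessment value as one would give a more precise arm comparison at no data cost, though the power gain is small on the protocol's own figures

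*Protocol*

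**What the plan says.** Protocol section 6.1 defines the endpoint: "The primary endpoint will be the change in composite clinical parameters of near point of convergence and positive fusional vergence", taken from the initial assessment to the outcome visits. Section 6.3.2 repeats it and fixes the method: "A repeated measures ANOVA will be used to assess the clinical parameters", together with a chi-squared test against published benchmarks. Neither test is given a covariate. The synopsis lists a Wilcoxon signed test, a paired t-test and Tukey post-hoc tests, again with none.

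The baseline values exist for every case subject. Section 5.1.3 describes "A standard optometric clinical exam that includes near point of convergence, positive fusional vergence" among its components. That examination is scheduled at the initial assessment (4.2.1) and at Outcome Visits 1 and 2 (4.2.5, 4.2.8). NPC and PFV also decide eligibility (3.4.2). Allocation is 1:1 in blocks (9.1.1), and no stratification on NPC or PFV is described.

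On size, section 6.4 says "The sample size calculation was performed using paired" t-tests, and continues: "Assuming 80% power, Alpha= 0.05, and adjusting for an 80% retention rate and 15% data loss due to motion artifacts during fMRI experiments". The resulting numbers are 37 (symptom score), 6 (NPC), 37 (PFV) and 46 (fMRI beta weight). The largest is rounded to 50 per arm. The same section expects 150 subjects to finish.

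**The concern.** Because the arms are randomised, their baseline means differ only by chance. A change score subtracts the whole baseline value, while the best prediction of the outcome from baseline usually has a slope below 1. The excess subtraction adds noise. It also moves the estimate when one arm happens to start worse, since subjects who start further from normal tend to move more by regression to the mean.

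At stake is precision, not validity. The change-based comparison of OBVAT+SCC with SCC alone is unbiased over randomisations, but its confidence interval is wider than the collected data require, and any one realised trial carries its own baseline imbalance.

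**Working it through.** **1. What the stated model tests.** Take two visits (initial assessment and Outcome Visit 1) and two arms. The group-by-time F statistic is the square of the two-sample t statistic on change. The protocol does not list the model's factors or levels, so this is a reading of 6.3.2. Outcome Visit 1 is the relevant visit because arm 2 starts OBVAT after it (4.2), so it is the only randomised comparison with SCC alone.

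**2. Variance.** Let s² be the variance at each visit, assumed equal, and rho the baseline-to-outcome correlation.
- Change score: 2s²(1 − rho)
- ANCOVA: s²(1 − rho²)
- Ratio: (1 − rho²) / [2(1 − rho)] = (1 + rho)/2

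The ratio of interval widths is √[(1 + rho)/2].

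| rho (assumed) | variance ratio | interval narrower by |
|---|---|---|
| 0.3 | 0.65 | 19% |
| 0.5 | 0.75 | 13% |
| 0.7 | 0.85 | 8% |
| 0.9 | 0.95 | 3% |

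**3. Chance imbalance.** With regression slope b and a realised baseline difference D between arms, the change-score contrast is expected to be the true effect plus (b − 1)D. For example, with b = 0.5 and D = 0.2 SD the shift is −0.1 SD. ANCOVA removes it.

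**4. Power if the change analysis has exactly 80%** (two-sided alpha 0.05, assumed because 6.4 does not give sidedness). Power = Φ[(1.960 + 0.842) × √(2/(1 + rho)) − 1.960].
- rho 0.3: 93.5% (gain 13.5 points)
- rho 0.5: 89.9% (gain 9.9)
- rho 0.7: 86.0% (gain 6.0)
- rho 0.9: 82.0% (gain 2.0)

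**5. Power on the protocol's own PFV figure.** The 37 cannot be reproduced independently, because 6.4 states no effect size, so the effect is back-solved. Evaluable subjects: 37 × 0.80 × 0.85 = 25. With the stated SD of the difference, 19, 80% power implies 2.802 × 19/√25 = 10.65 (11.1 with the exact paired t). Holding that effect fixed, the change analysis has power Φ[2.802 × √(n/25) − 1.960], and ANCOVA multiplies the first term by √(2/(1 + rho)).

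| n per arm | origin | change analysis | gain, rho 0.7 to 0.3 |
|---|---|---|---|
| 34 | 50 × 0.68 | 90.4% | 3.9 to 7.7 |
| 40 | 50 × 0.80 | 94.3% | 2.7 to 4.9 |
| 50 | planned | 97.7% | 1.3 to 2.1 |
| 75 | 150/2 | 99.8% | 0.1 to 0.2 |

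The exact paired t gives 3.7 to 7.3 points at 34, 2.5 to 4.4 at 40, 1.1 to 1.7 at 50 and about 0.1 at 75. Treating the arms as independent, with the per-arm SD implied by 6.4 (19/√(2 × 1.4) = 11.35), puts change-analysis power at about 98% already at 34 per arm, which leaves less to gain. NPC was said to need only 6 subjects, so on 6.4's own calculation it too exceeds 80%. Its effect back-solves unstably (2.8 to 4.3 with 4 evaluable).

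**6. Effect of the eligibility limits.** Write outcome = a + b × baseline + e. The change-score variance is var(e) + (1 − b)² × var(baseline). Start with unit variances and b = 0.5, so var(e) = 0.75 and the ratio is 0.75. Truncating a normal baseline at its mean cuts its variance to 0.363. The ratio becomes 0.75/(0.75 + 0.25 × 0.363) = 0.89, although rho falls to 0.33. The interval gain drops from 13% to about 6%, and the power gain from 80% drops from 9.9 to about 4.3 points.

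**The case against.** The strongest reply is that nothing in 6.3.2 is wrong. A repeated measures ANOVA of a change endpoint is valid under randomisation, and covariates are often left to a statistical analysis plan, which is not at hand. This stands in part: the point is about efficiency, not error. It does not dispose of the matter, because 6.3.2 goes beyond silence and fixes a named method, and an analysis plan that followed it as written would inherit the less precise estimator.

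A reader might go further in four ways that the documents do not support.
- *Baseline is ignored.* It is not. The endpoint is change from the initial assessment, so baseline enters by subtraction or as a repeated level. What is missing is its use as a covariate.
- *The trial gives up 6 to 13 points of power.* That needs exactly 80% starting power for NPC and PFV. Section 6.4 sizes the trial on the fMRI beta weight and puts the need at 6 for NPC and 37 for PFV. Nor is the gain the same at every sample size: it looks constant only if the effect is reset to give 80% at each n.
- *Restricted entry values of NPC and PFV make the change score worse still.* Step 6 shows the opposite: truncating baseline brings the two analyses closer.
- *The correlations in 6.4 supply rho.* They are tied to an OBVAT-minus-placebo difference in typically occurring CI, not to baseline and outcome in one subject.

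On the other side, the high power implied by 6.4 is itself uncertain. No effect size is given, the pilot population and comparator differ from this trial's, and a paired test is applied to parallel arms.

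**Conclusion.** The point holds as an efficiency recommendation. The stated analysis, read as initial assessment against Outcome Visit 1, is less precise than ANCOVA for any rho below 1 when variances are equal. For an assumed rho of 0.7 to 0.3 the intervals would be about 8% to 19% narrower, and less if eligibility limits have reduced the baseline variance. The precision gain does not depend on sample size, but the power gain does. It is about 4 to 7 points at 34 per arm, 1 to 2 at 50 and near zero at 75 on the effect implied by the PFV figure. It reaches 6 to 13 only from a starting power of exactly 80%.

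These sizes rest on an assumed rho, two-sided alpha, equal variances at the two visits, and the SD and attrition figures of 6.4 carried over as they stand.

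**What to change.** In 6.3.2, compare the arms on NPC and PFV (or their composite) at Outcome Visit 1 with a linear model containing arm and the initial-assessment value of the same measure. A mixed model that constrains the arms to a common baseline mean is an equivalent choice, and it can also keep subjects with a missing visit, in line with the intention-to-treat statement in that section.

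The benchmark analysis may stay as a chi-squared test. Logistic regression on baseline NPC and PFV with a standardised risk difference is an optional refinement.

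The cost is a wording change and one degree of freedom per covariate. No new data, visits or subjects are needed.
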